#### Follow-up 1 (4–6 weeks postoperatively)

NE, GCS, mRS, GOS, Markwalder scoreVital parameters (BP, SAT, HR)cCT scan (MLS, hematoma width, recurrence)

#### Follow-up 2 (6 months postoperatively)

NE, GCS, mRS, GOS, Markwalder score (Fig. 2)

**Fig. 2 Fig2:**
[figure not shown]
Study schedule

### Statistical consideration

#### Number of participants with rationale

A systematic review by Almenawer et al. [23] reported an overall recurrence rate of approximately 10.7% for cSDH in the normal population. According to the literature, recurrence rates in the normal population range from 5% to 30% [24]. Recurrence rates have been described to reach 33% under antithrombotic therapy with ASA [12, 14]. In a retrospective study we conducted in patients where ASA treatment was continued, a recurrence rate of 22% was observed [15]. Based on the available data from the literature, we hypothesized that the recurrence rates after burr-hole drainage of cSDH under ASA treatment (π_ASA_) and without ASA treatment (under placebo, π_Placebo_) are 28% and 10%, respectively. The sample size was set to ensure at least 80% power (1 – β = 0.8), at a significance level of α = 5%. The sample size was estimated using a resampling procedure in which different sample sizes were each evaluated 999 times by drawing random samples of events based on these assumptions. This indicated that randomizing 142 patients should allow us to show the assumed difference in event rates between the groups.

The primary analysis will be performed on the full analysis set – consisting of all patients who are randomized to the study, regardless of protocol violations – and based on the intention to treat principle. The primary analysis is a comparison of incidence rate. The difference in incidence rate will be tested and a 95% confidence interval for the difference constructed. In case of many losses to follow-up, inverse probability censoring weights will be used to deal with missing outcome data. A sensitivity analysis will be performed on the per protocol analysis set. In the primary analyses, the type-I error rate for significance will be taken as α = 0.05. As secondary analysis, a time-to-event analysis will be performed comparing the hazard of recurrence between treatment arms using a Cox proportional hazards model. Secondary outcomes will be analyzed using generalized linear regression models with appropriate distribution family, depending on the outcome (binomial for binary outcome, Poisson for counts, Gaussian for continuous, normally distributed, outcomes).

#### Randomization

Each eligible patient will be allocated to ASA or placebo group either on the first postoperative day (in case of emergency operation on the same day), or preoperatively (in case of emergency operation 24 h after last ASA intake, or in case of elective surgery 5 days before operation).

Randomization will be performed by an independent individual using an unstratified block randomization procedure as implemented in the electronic data capture software SecuTrial. An allocation ratio of 1:1 and a block size of 8 will ensure a balance in sample size across both groups over time.

#### Methods of minimizing bias

Double-blind randomization in 1:1 allocation should reduce any bias due to patient or physician expectations. Randomization will be performed using a computer system (SecuTrial) through an independent individual. The medication will be numerically labelled at the Pharmacy of the University Hospital of Basel and will then be provided to the ward and applied to the patient. This will allow a double-blinded randomization (patient and treating physician will be blinded to the treatment). The placebo and ASA medications will be put into blisters so that they cannot be distinguished in their appearance. Data will be checked for protocol violation by the monitoring institution.

Throughout the trial, case report form (CRF) information will be inserted into a software especially designed for clinical trials (SecuTrial), through which mistakes are decreased to a minimum. At the end of the trial, the CRF data input will be verified by two individuals.

#### Blinding procedures

The study medication (ASA or placebo) will be provided as similar looking medication in blisters. The medication will be packed by the Pharmacy of the University Hospital of Basel and will be numerically labelled. The corresponding randomization list will be uploaded to the electronic data capture (EDC) system by the responsible Data Manager at the Clinical Trial Unit (CTU) Basel.

#### Unblinding procedures (Code break)

In case of problems that cannot be solved with ongoing randomization (safety concerns, withdrawal of participation, etc.), the participant’s allocated intervention will be revealed. Unblinding can be performed by authorized persons using the EDC system or by contacting the Pharmacy of the University Hospital of Basel. Each unblinding is documented and reported to the principal investigator. In case of a thrombotic event, ASA will be resumed regardless of the study arm in which the patient is allocated.

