### Outcomes

#### Primary study outcome measures

The primary study outcome measure is recurrence of cSDH requiring revision surgery within 6 months.

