### Statistical analysis

#### Datasets to be analyzed, analysis populations

The full analysis set (FAS) will include all randomized patients and will be analyzed based on the intention to treat principle.

The per protocol set will include all patients of the FAS who had complete follow-up and who did not have serious protocol violations. Patients receiving the opposite treatment than that to which they were randomized will be excluded from this set.

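### The code-break rule lists withdrawal of participation as grounds for revealing the arm, although withdrawn patients stay in the full analysis set and the endpoint depends on a decision to reoperate

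*Protocol article*

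**What the plan says.** The section Unblinding procedures (Code break) of the protocol article begins "In case of problems that cannot be solved with ongoing randomization (safety concerns, withdrawal of participation, etc" and continues that "the participant’s allocated intervention will be revealed". In the bracketed list, "safety concerns, withdrawal of participation, etc", withdrawal thus stands beside safety concerns, and the list is left open at its end. No condition ties the code break to a need to know the arm. The same section adds: "Each unblinding is documented and reported to the principal investigator".

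Four other statements bear on this:

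- **Methods of minimizing bias:** the safeguard is that "patient and treating physician will be blinded to the treatment".
- **Datasets to be analyzed:** "The full analysis set (FAS) will include all randomized patients and will be analyzed based on the intention to treat principle".
- **Primary study outcome measures:** the endpoint is "recurrence of cSDH requiring revision surgery within 6 months".
- **Data collection and follow-up for withdrawn participants:** these patients return to the trial's outpatient clinic at 4–6 weeks, but are described as non-participants.

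**The concern.** A patient can withdraw without anyone needing to know the arm. The rule nevertheless names withdrawal as an instance in which the allocation is disclosed.

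The endpoint is exposed to such knowledge because it is not a laboratory value or a death. It requires someone to decide that a recurrence needs another operation. The article names no operative threshold and no blinded adjudication, so blinding of patient and physician is the protection it offers. The Background says that most surgeons prefer to stop antiplatelet therapy because they fear recurrence or bleeding, so knowledge of the arm could plausibly affect readiness to reoperate. Study medication lasts 12 days, so most of the six-month endpoint window is still ahead for a patient who withdraws during treatment.

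At stake is differential ascertainment of the primary endpoint in a subset of the analysed patients. The cause would be a disclosure that serves no stated purpose.

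**Working it through.** **1. The plan's own figure.** The sample size section gives 28% versus 10%, 80% power, α = 5% and 142 patients. With the unpooled two-proportion formula, two-sided:

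n = (1.960 + 0.842)² × (0.28 × 0.72 + 0.10 × 0.90) / 0.18² = 70.6, so 71 per arm and 142 in total.

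The stated figure is reproduced and is not affected by this point. It supplies the 71 per arm used below.

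**2. The chain in the text.** Withdrawal is an example of a trigger (Unblinding procedures). A withdrawn patient stays in the full analysis set (Datasets to be analyzed). The patient is seen again in the same clinic (follow-up for withdrawn participants). The endpoint needs a decision to reoperate (Primary study outcome measures). One link is missing: no section says whether a reoperation after withdrawal counts in the primary analysis. Steps 3 to 5 apply only if it does.

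**3. Assumptions for size.** None of these is in the documents:

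- share unblinded on withdrawal: w = 5%, 10% or 15%, which is about 7 to 21 of 142 patients;
- true rate in both arms: 15% (no treatment effect);
- relative shift in reoperation once the arm is known: k = 20% or 30%, upward under ASA and downward under placebo;
- all outcomes after withdrawal are counted.

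**4. Formula.** ASA rate = 0.15 × (1 + wk); placebo rate = 0.15 × (1 − wk); false difference = 2 × 0.15 × wk = 0.30 × wk. The rejection rate comes from exact binomial enumeration at 71 per arm, rejecting when the two-sided 95% Wald interval for the difference excludes zero.

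| w | k | ASA vs placebo rate | False difference (points) | Rejection rate |
|---|---|---|---|---|
| 0 | – | 15.0% vs 15.0% | 0 | 4.98% |
| 5% | 20% | 15.15% vs 14.85% | 0.30 | 5.0% |
| 5% | 30% | 15.225% vs 14.775% | 0.45 | 5.0% |
| 10% | 20% | 15.3% vs 14.7% | 0.60 | 5.1% |
| 10% | 30% | 15.45% vs 14.55% | 0.90 | 5.2% |
| 15% | 20% | 15.45% vs 14.55% | 0.90 | 5.2% |
| 15% | 30% | 15.675% vs 14.325% | 1.35 | 5.5% |

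The largest false difference, 1.35 points, is 1.35 / 18 = 7.5% of the planned difference of 18 points.

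**5. Sensitivity to the assumed shift.** Replace the relative shift by an absolute one of 5 to 10 percentage points in each direction, again at 5–15% unblinded. The false difference becomes 0.5 to 3.0 points. The rejection rate becomes 5.4–9.3% at a 10% base rate (baseline 5.3%) and 5.2–7.5% at a 19% base rate (baseline 5.1%). The top value is an extreme: at a 10% base rate, a 10-point shift means that unblinded placebo patients are never reoperated and unblinded ASA patients twice as often.

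**The case against.** The strongest reply is that the rule is narrower than its bracket. It opens with problems that cannot be solved while the allocation stays blinded, so it can be read as covering only withdrawals that create such a problem. A reader might infer that every withdrawal must be unblinded; the text does not go that far. What stands is that withdrawal is offered as an example of such a problem, and nothing says when it is one.

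Second, membership of the full analysis set does not by itself mean that outcomes after withdrawal are used. Withdrawn patients are followed as non-participants, only a 4–6 week visit is described for them, and censoring weights are foreseen if losses are many. If their later outcomes are not used, unblinding at withdrawal cannot bias their own endpoint, and the issue becomes one of missing data. This objection stands, and it is why the point is conditional.

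Third, the documents do not say that the surgeon who decides on revision learns the arm. Disclosure goes through authorized persons or the pharmacy, with a report to the principal investigator. This also stands, although the rule does not keep the arm from the treating physician either.

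A reader might further infer that revealed arms allow prediction of later allocations, since the article states that "a block size of 8 will ensure a balance in sample size across both groups over time". The documents do not support this. An enrolling clinician would need the revealed patient's position in the list and the block boundaries, and would have to learn the arm before the block filled. Allocation is made by an independent individual through the data capture system, and nothing shows that anyone who enrols patients has that information.

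**Conclusion.** The point holds in a limited form. The article states a trigger that is wider than any purpose it gives, and in doing so it weakens its main stated protection for a judgement-dependent endpoint. Bias in the primary comparison follows only if outcomes after withdrawal are counted and the arm reaches those who decide on reoperation; the article settles neither.

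Under the main assumptions the size is modest, and type I error hardly moves from its baseline. Larger effects need strong assumed shifts. The direction is also assumed: if knowledge of ASA made surgeons more reluctant to operate again, the false difference would change sign. With no withdrawal rate in the documents, these figures show a range and are not estimates. The case for the change is that the present wording gains nothing and the correction is cheap, not that the trial's result is in serious danger.

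**What to change.** In Unblinding procedures, delete withdrawal of participation and the open-ended remainder from the list of triggers. State that the allocation is revealed only when knowing the arm is needed for the patient's care, and that withdrawn patients and their physicians otherwise stay blinded.

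Reconcile that section with the follow-up of withdrawn participants and the definition of the full analysis set. Say which outcomes after withdrawal enter the primary analysis, and how the remaining window up to six months is handled for these patients.

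An analysis restricted to endpoints decided before any code break is at most a supportive check. Code breaks made for safety may be related to the outcome, so discarding what follows them brings its own selection bias.

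The cost is a protocol amendment of a few sentences. No extra patients, visits or staff are needed.

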#### Compliance with study intervention

During hospitalization, compliance will be monitored by study nurses. After hospital discharge, patients will be instructed to continue taking medication until the 12th postoperative day. Compliance during the ambulatory phase of the trial will be controlled by patient or caregiver interviews during the clinical follow-up after 6 weeks. The patients will be explicitly asked if they took the study medication up to the 12th postoperative day and the empty blister and the rest of the medication, if there is one, will be collected. In case of non-compliance, a note-to-file will be completed and taken into account in the final statistical evaluation.

#### Data collection and follow-up for withdrawn participants

Withdrawn patients will be clinically followed up as non-participants, 4–6 weeks postoperatively in our outpatient clinic.

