#### Primary analysis

The difference in recurrence rate (π_Asp_–π_placebo_) will be tested by calculating a two-sided 95% confidence interval of the difference in proportions. Inverse probability censoring weights will be used to prevent selection bias in case of many losses to follow-up. The analysis will be performed primarily on the FAS. Sensitivity analyses will be performed on the per protocol set.

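### Withdrawn patients are given no 6-month outcome assessment, although the primary endpoint runs to 6 months and is analysed by intention to treat

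*Protocol article*

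**What the plan says.** In the protocol article, the section on data collection and follow-up for withdrawn participants is one sentence: "Withdrawn patients will be clinically followed up as non-participants, 4–6 weeks postoperatively in our outpatient clinic".

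The primary outcome is "recurrence of cSDH requiring revision surgery within 6 months". On the analysis population, the Statistical analysis section states: "The full analysis set (FAS) will include all randomized patients and will be analyzed based on the intention to treat principle". The sample-size section adds that protocol violations do not remove anyone from this set.

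Two sentences deal with missing outcomes. The Primary analysis section says: "Inverse probability censoring weights will be used to prevent selection bias in case of many losses to follow-up". The section on missing data and drop-outs says instead that the last available observation is used.

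The Unblinding procedures section names withdrawal among its examples: "safety concerns, withdrawal of participation, etc.), the participant’s allocated intervention will be revealed". The clause is conditional, because it covers problems that cannot be resolved while the allocation stays concealed. The section on minimizing bias relies on patient and treating physician being blinded.

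**The concern.** An intention-to-treat comparison of 6-month revision rates needs the 6-month status of every randomized patient. The only follow-up stated for withdrawn patients stops at 4–6 weeks, and calling them non-participants leaves it unclear whether even that visit yields trial data. The outcome is then missing because of a rule, not because the patient could not be reached.

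The loss matters for two reasons. The trial is sized at almost exactly 80% power with no stated allowance for lost outcomes. And if withdrawal is related to both arm and outcome, the comparison of the remaining patients is no longer protected by randomization.

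There is a smaller, linked issue. If an allocation is revealed because of withdrawal while the 6-month window is open, someone who helps to decide on or classify a reoperation could learn the arm. The endpoint includes a decision to reoperate, so it is sensitive to that knowledge.

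**Working it through.** **1. Is there a 6-month outcome for withdrawn patients anywhere?**

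- Withdrawn-participants section: one visit at 4–6 weeks.
- Follow-up 2 (6 months): part of the participants' schedule, and nothing extends it to those labelled non-participants.
- Follow-up of (serious) adverse events: 4–6 week and 6-month documentation, but only once an intracranial bleeding has been diagnosed. It does not find a late recurrence in a withdrawn patient.

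The answer is no. Taking 4–6 weeks as 1 to 1.5 months, the unobserved part of the window is (6 − 1.5)/6 = 75% to (6 − 1)/6 = 83%. This is calendar time, not a share of events, because the documents do not say when recurrences occur.

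**2. Does the analysis repair the gap?**

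- Censoring weights are used only if losses are many, with no threshold. They also assume that measured covariates explain who is lost.
- The last-observation rule would record a patient without recurrence at 6 weeks as having none at 6 months.
- The per protocol set requires complete follow-up, so the sensitivity analysis drops the same patients.

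**3. Reproducing the plan's sample size.** Inputs from the sample-size and Primary analysis sections: 28% (ASA), 10% (placebo), two-sided 5%, power 80%. The allocation, 1:1, is in the Randomization section. With the unpooled formula,

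n per arm = (1.960 + 0.842)² × (0.28×0.72 + 0.10×0.90) / 0.18² = 7.85 × 0.2916 / 0.0324 = 7.85 × 9 ≈ 70.6, so 71 per arm and 142 in total.

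The plan's 142 is reproduced. Exact enumeration at 71 per arm gives 80.2% power for both the Wald and the pooled z test, so there is no reserve.

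**4. Power if outcomes are missing.** The missing shares are assumptions. Number per arm = 71 × (1 − share), rounded; exact power at 28% versus 10%:

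| Missing (assumed) | n per arm | Wald | Pooled z |
|---|---|---|---|
| 0% | 71 | 80.2% | 80.2% |
| 5% | 67 | 79.3% | 77.4% |
| 10% | 64 | 77.2% | 75.2% |
| 15% | 60 | 74.4% | 72.5% |
| 20% | 57 | 72.2% | 71.4% |

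**5. Bias if a 6-week non-event is carried forward.** Let w be the share withdrawn in an arm and f the share of recurrences after the 4–6 week visit (both assumed), with withdrawn patients at the same risk as the rest of their arm. The recorded rate is p × (1 − w × f). The true difference is 28 − 10 = 18.0 points.

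- w = 10% in both arms. f = 10%: 27.72 − 9.90 = 17.8 points. f = 50%: 26.6 − 9.5 = 17.1 points.
- w = 15% on ASA, 5% on placebo. f = 10%: 27.58 − 9.95 = 17.6 points. f = 50%: 25.9 − 9.75 = 16.2 points.
- w = 5% on ASA, 15% on placebo. f = 50%: 27.3 − 9.25 = 18.05 points, practically unchanged.
- w = 20% in both arms. f = 10% to 50%: 17.6 to 16.2 points.

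Under these assumptions the bias is small at low withdrawal. It grows when withdrawal is frequent or is concentrated in the ASA arm.

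**The case against.** The strongest reply is that the gap is narrow and that several larger inferences do not follow.

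- A reader might infer that anyone who stops the tablets is dropped. The text does not support that. The compliance section handles missed medication by a note-to-file and a check at the 6-week follow-up, and protocol violators stay in the full analysis set. The withdrawn-participants sentence reads most naturally as leaving the trial. What stands is that withdrawal is not defined, so a patient who leaves the intervention but would allow further data collection has no stated route to 6 months.
- A reader might infer that revision surgery after week 6 goes unrecorded for all patients, because the 6-month visit lists only clinical scores. The recurrence item at day 1 and 4–6 weeks is a CT reading, and no CT is listed at 6 months. The study schedule figure and case report form are not shown, and the planned Cox analysis presupposes dated recurrences. That inference should not be drawn.
- A reader might infer that each withdrawal unblinds the surgeon. The code-break clause is conditional, limits access to authorized persons, and provides a report to the principal investigator. It does not say that the operating surgeon is told. What stands is that withdrawal appears as an example without a limit, which sits poorly with the stated blinding.
- A reader might suppose that withdrawals follow bleeding or thrombotic events. The documents do not say so. They give such events their own follow-up and do not call them withdrawals.
- Censoring weights are planned, so missing outcomes are not ignored. That is fair, but the trigger is undefined and the last-observation rule points elsewhere. A modelled outcome is also a poor substitute for one that a telephone call could obtain.
- Patients who refuse all further data use cannot be followed. That is correct, and no amendment changes it.

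**Conclusion.** The point holds in limited form. It rests on a stated rule, not on detail left to a fuller document: withdrawn patients have a 4–6 week clinical visit and no 6-month outcome, in a trial whose primary endpoint runs to 6 months and whose primary analysis covers all randomized patients. Some of the resulting missing data are avoidable, and neither planned method for missing outcomes reliably repairs them.

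The size cannot be fixed from the documents, which give no withdrawal rate and no timing of recurrence. The power loss and the bias shown above are illustrations under assumed values. If few patients withdraw, and at similar rates in both arms, the effect is minor. No figure in the protocol is wrong on this point, and the sample size of 142 stays as it is. This is an inexpensive improvement to design and conduct, not an error that invalidates the trial.

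**What to change.** Amend the section on withdrawn participants:

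1. Define withdrawal. Patients who stop study medication or leave the intervention without withdrawing consent to data use remain in follow-up to 6 months and are analysed in their randomized arm.
2. For patients who withdraw from further participation, ask permission to obtain revision-surgery status (with date) and vital status at 6 months, by telephone or from records, and use these in the full analysis set.

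Reconcile the code-break section with the blinding section. State that withdrawal alone does not trigger a code break, and that any code break is kept, where possible, from those who judge the endpoint. Code breaks for safety are not affected.

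The cost is amendment wording and a call or record check per withdrawn patient; at the assumed 5% to 20% of 142, that is about 7 to 28 patients. It should be settled prospectively, because status not sought at 6 months may not be fully recoverable later.
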